### Motor function

Following the physical examination and in case of no contraindications, functional outcomes are assessed in a standardized order at each visit. Following consensus discussions and in order to prevent muscle fatigue prior to torque assessment, the order is as follows: (1) posturography, (2) jumping assessment, (3) kinematics, (4) clinical testing, (5) strength. If a functional assessment is done for both the left and right side, side order will be randomized. Randomization sequence is generated using a computer-based algorithm (www.randomization.com). For standardizing purpose (setting and device familiarization) and to avoid bias, one demonstration (by the investigator) and one test run are completed before each new biomechanical outcome assessment start. A numerical rating scale (NRS, 0–10 points Likert scale) is used to assess actual pain prior to and following the motor function assessment.

#### Posturography

Postural control in single and bipedal stance is assessed using balance boards (Wii Balance Board, Nintendo, Kyoto, Japan; modified by CSMi Computer Sports Medicine Inc., Stoughton, MA, USA). Postural sway is estimated by the trace length [mm] of the excursion of the centre of pressure (COP). For the measurement, participants were asked to maintain in upright stance as still as possible for 30 seconds without wearing shoes, with their hands on their hips and their eyes open, standing on two balance boards. Afterwards, the single leg stands (left and right) followed in the randomized order (each 30 s, eyes open, one single balance board) with the contralateral knee bend (90°).

In comparison to a laboratory-grade force platform and with an intraclass correlation (ICC) of 0.81 (single limb stance, 95 % CI 0.39–0.92) and 0.77 (double limb stance, 95 % CI 0.69–0.95), respectively, the Wii balance board shows a sufficient validity [29]. Accordingly and with an ICC of 0.89 (95 % CI: 0.76–0.95) for single limb balance assessments and an ICC of 0.86 (95 % CI: 0.54–0.9) for bipedal stance, a high reproducibility was shown [29].

#### Jumping assessment

Jumping ability is afterwards determined using the same balance boards. Countermovement jumps (CMJ) and combined CMJs followed by reactive jumps are executed. Whilst each participant performs double leg jumps, single leg jumps are, for security purpose, performed by athletes only.

After warm-up (30 s tapping on a stepper with a 14–21 cm high) and familiarization, participants perform two bipedal CMJs, followed by two combined bipedal CMJs/reactive jump. For the reactive jumps, all participants are told to immediately add another jump after landing from the CMJ. All athletes afterwards jump twice with the left and twice with the right leg (randomised order), each time starting with a CMJ followed by a CMJ with a reactive jump. Main outcomes will be jumping height in cm for the CMJ and contact time [ms] for the reactive jumps.

The balance board is able to precisely (*r* = 0.99 in comparison to gold standard laboratory-grade force platform) measure vertical ground reaction force and thus jumping performance [30]. Data from both the posturography and the jumping tests are stored for the later analysis using the HUMAC Balance program (CSMi Computer Sports Medicine Inc., Stoughton, MA, USA).

#### Kinematics

A non-invasive external three-dimensional wireless movement analysis system (IMU sensors, Ergotest Innovations, Porsgrunn, Norway) with a 200 Hz sample rate is used to collect kinematic data. Sufficient test–retest reliability of this measurement system for lumbar spine kinematics (*r*
^2^ > 0.97; RMSE = 4.1°; *p* < 0.001) has recently been demonstrated [31]. Six sensors are attached, two on the lower back (each 5 cm left/right from L3), two on the pelvis (left and right iliac spines), and two on the thigh, each 10 cm above the medial tibia plateau. Participants perform over the maximal range of motion in a self-determined and comfortable velocity with eyes open. After familiarization trial and device zeroing, all subjects perform two times maximal spine flexion-extension movements, followed by maximal lateral flexion movements (two times), followed by two maximal rotation movements (side order randomised). Maximal ranges of motion (ROMs) [°] will be selected for further analysis.

Data were stored on a data processor for the following offline analysis. Maximal ROM was computed from raw data using MuscleLab Professional (Ergotest Innovations, Porsgrunn, Norway).

#### Clinical testing

The Timed Up and Go test (TuG) for mobility testing and the Chair Rise Test (CRT) for lower extremity strength/force are performed during clinical function testing [32]. For the TuG, subjects will sit on a chair with arm support, stand up, walk straight 3 m to a mark on the floor, turn around, walk back to the chair and sit down again. Participants then (CRT) are set on a chair (46 cm sitting height, arms crossed in front of the breast) and are asked to stand-to-sit five times as fast as possible without losing control.

Time [s] is the outcome further analysed for CRT and TuG; common stopwatches are used to assess it. Both tests are performed twice; the best result will be selected for further analysis.

#### Torque/strength

Maximum trunk extension strength assessment with isokinetic or, depending on the participating centres’ isokinetic device availability, isometric maximum trunk extension torque testing [Nm] is considered to be the primary outcome. To obtain maximal torque (isokinetic, *n* = 4 study sites) or maximum isometric voluntary force (isometric, maximal isometric voluntary force (MIVF), *n* = 2 study sites) of the trunk extensors (primary outcome) and flexors, validated devices from various but nevertheless renowned producers are used.

After a specific warm-up with 30 isokinetic repetitions at 60°/s (isometric: two submaximal practice trials), five (three) tests at 60°/s (3 s) were performed, separated by 2-min rest intervals. Ranges of motions (isokinetic) are device-specific set to 40–45° in flexion and 10–15° in extension. Subjects were verbally encouraged in a standardized way to elicit maximal effort. Collected data were immediately analysed and the highest torque (force) was considered to be representative for further statistical analysis.

### Intervention

#### Therapy flow and phases

All interventions are guided (centre-based) or instructed (home-based) by trained and experienced medical training or sports therapists. Following the randomization at the end of M1, intervention group participants are scheduled to a 3-week centre-based guided intervention, followed by a 9-week home-based individual training. In each phase and in accordance with the guidelines [33], intervention participants are told to train three times a week with a mean duration of 30 minutes. The program consists of four different sensorimotor exercises. For individualization purposes, all exercises comprise 12 different levels and offer the possibility to add self-initiated additional motor tasks like ball tapping (single-handed, on the floor or against the wall and/or additional weight). Two of the exercises are dedicated to directly train the core stabilizing and/or core surrounding muscles whilst the two other exercises are considered to impact indirectly on the upper and/or lower extremities. The exercises are commonly described as: (1) quadrupedal/all-fours stability; (2) deadlift/rowing; (3) double leg–single leg heel-pad stance; (4) side planks. Exercises will be performed with three series of ten repetitions each. In between series, a 2-minute break (self-controlled) is held. Details on the intervention and belonging levels are provided in Table 1.

**Table 1 Tab1:** Interventional exercises details. For each exercise, level (1–12), surface (stable/instable) and description are provided

Exercise 1: quadrupedal/all-fours stability		Exercise 2: deadlift/rowing		Exercise 3: double leg – single leg heel-pad stance		Exercise 4: side planks	
Stable ground	Instable ground	Stable ground	Instable ground	Stable ground	Instable ground	Stable ground	Instable ground
1. Hand and knee stance: Bending, stretching a leg 2. Hand and knee stance diagonal arm and leg: from body centre upwards (horizontal) 4. Hand and feet stance: bending, stretching a leg	3. Hand and knee-stance diagonal arm and leg: from body centre upwards (horizontal) 5. Hand and feet stance: bending, stretching a leg 6. Hand and feet-stance: diagonal arm and leg: from body centre upwards (horizontal) 7. Hand and feet-stance: release arm, trunk rotation 8. Planks: leg horizontal 9. Planks: diagonal leave arm and leg 10. Planks: leave arm, rotate trunk 11. Planks: leave arm and diagonal leg, rotate trunk 12. Press-up: leave arm	1. Rowing plus additional weight 3. Rowing in ball stance plus additional weight 5. One handed rowing plus additional weight 6. One handed rowing plus additional weight In ball stance 9. One handed rowing plus additional weight in single leg stance 10. One handed rowing plus additional weight In single leg ball stance	2. Rowing plus additional weight 4. Rowing in ball stance plus additional weight 7. One handed rowing plus additional weight 8. One handed rowing plus additional weight In ball stance 11. One handed rowing plus additional weight In single leg stance 12. One handed rowing plus additional weight In single leg ball stance	1. Bipedal: heel-pad-stance 3. Unipedal stance plus hip abduction 4. Unipedal stance plus hip abduction and leg extension 6. Unipedal ball stance plus hip abduction and leg extension 10. Unipedal squat 11. Unipedal squat plus additional weight	2. Bipedal: heel-pad-stance 5. Unipedal stance plus hip abduction and leg extension 7. Unipedal ball stance plus hip abduction and leg extension 8. Squat in ball stance 9. Squat in ball stance and hip bending 12. Squat in ball stance with additional weight	1. Knee on ground; hip released from ground 2. Knee on ground; hip stable 3. Knee on ground; hip up/down 5. Legs stretched, hip fixed upwards 8. Legs stretched, release leg from ground 10. Legs stretched, release leg and diagonal arm from ground: horizontal-contact 12. Legs stretched, hip upwards, release leg and diagonal arm from ground: horizontal-contact	4. Knee on ground; hip up/down 6. Legs stretched, hip fixed upwards 7. Legs stretched, hip up/down 9. Legs stretched, release leg from ground 11. Legs stretched, release leg and diagonal arm from ground: horizontal-contact

#### Individualization

For individualization purposes, the level (including the number and type of self-initiated additional motor tasks and additional weight) for each of the four exercises is determined by an experienced therapist at the beginning of the intervention for all participants in the intervention group. The therapist in charge rates the participants’ performance accuracy at level one and derives a starting level. Performance accuracy is thereby standardized rated based on the axis and plane alignment (extremities, trunk) during motion, movement goal (endpoint) accuracy and no loss of balance during motion or single movements order. The starting level is defined as the highest level in which this accuracy can be reached. This level (including the number and type of self-initiated additional motor tasks and additional weight) is further adaptive and may be corrected in both directions (increase or even decrease in level) continuously by the therapist during the centre-based phase. The goal for the intervention is to increment by one level once a week until the maximum level 12 is reached.

The intervention group patients receive individualized exercise counselling for home-based training as follows: at the end of the centre-based trainings, the starting level for the home-based phase is determined (therapist in collaboration with the participant). In addition, the goal level for the home-based phase is determined. Each subjects’ goal level and the periodization to reach this level is subsequently recorded on the training log. Intervention group subjects were additionally encouraged to contact the counselling exercise therapist by phone, e-mail or in person at any time during the home-based intervention. Final therapy individualization may be accomplished by using a standardized procedure to detect potential non-responder and/or non-complier. This detection is based on cutoff values which will be determined from the studies’ questionnaires. If a potential non-responder and/or non-complier is detected, each study site is recommended to implement an additional behavioural module to the intervention. This module and its empirical funding is described in detail elsewhere [34].

Control group participants do not receive any additional intervention in/from one of the study centres but may proceed with their regular care (e.g. physiotherapy or manual therapy) or additional interventions (the same applies to the intervention group) if they are engaged in one at the time of study inclusion. The intervention within medicine in spine exercise (MiSpEx) thus can be seen as additive.

#### Therapy monitoring

During the stationary centre-based phase, a standardized training log is completed by the therapist, documenting the exercise level and the (if applied) additional weight. To monitor home training compliance, intervention group patients are asked to fill in an exercise log during the home-based training (between M2 and M3).

### Statistical analysis

Data is collected and analysed centrally after assessment completion. Following visual and physiological range plausibility control, a gain score analysis (change score analysis) using the mean difference between M1 and M3 for between-group differences of the primary outcome is performed.

Hypotheses testing for all other measurement times and secondary outcomes are performed using particular fitting regressional and variance analytical testing. Potential mediators and confounders like the amount of physical activity, psychosocial scores, age, gender, initial pain level and body weight will be analysed using multiple regression mediating analyses [35] or included into variance analyses as covariates. For mediation analyses, total as well as direct and indirect effects are calculated. Sobel testing and 95 % confidence interval (CI) bias corrected bootstrapping (n_sub-samples_ = 10,000) are conducted for indirect effect quantification [36–38].

All statistical procedures are executed after the examination of underlying assumptions for parametric or rather non-parametric hypotheses testing. Due to the explorative analyses of the secondary outcomes, no alpha-error adjustment is performed. To increase statistical power, missing values are multiple imputed using standardized procedures [39] and only following (in case of psychometric scores) specific test manuals. The one-sided a priori level of significance is set at α = 0.025 for all statistical analyses.

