### Participants

#### Sample size determination

A pilot feasibility study was conducted (unpublished material). The therein found outcome with the largest effect size was selected as the primary outcome for the present study. Thus, primary outcome is maximal back extension torque. Sample size calculation was based on the effect size of d = 0.24 (based on the changes in primary outcome from baseline to post-intervention (12 weeks)). For the main study, effect size was conservatively completed to d = 0.2.

Participants are allocated to intervention or control group at the ratio of 2:1. Normal distribution and variance equality are assumed. Following a determined α-error probability of 2.5 % and a β-error probability of 0.1, a minimal sample size of 1186 patients are consequently to be included into analysis (*n* = 791 in the intervention and *n* = 395 in the control group). As a dropout rate of 30 % is assumed, a total of *N* = 1542 participants are included in the study. Although motor control and stabilizing exercise are likely to show equal effects for the general population and for top athletes [15], medical access and the potential to implement medical exercise regimes into everyday life differ between these populations (e.g. training schedule, competitions). According to study aim 1, and beside the studies’ main target group, we make additional effort to also recruit a sample of athletes to gain further (beyond the main analyses) insight and test the feasibility in this much less investigated population. For dichotomization purpose, only top competitive athletes (A to D pool, participating in top level international, federal or state competitions) are further treated as athletes.

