### Experimental procedure

In this multicentre intervention trial, a 12-week sensorimotor intervention is performed (3 weeks supervised centre-based followed by 9 weeks home-based) after the randomization (intervention group only). The control group does not receive any (additional) therapeutic or placebo treatment during this period. Each participant is scheduled for five measurement visits (M1-M5) prior to (M1) and following centre-based (M2), following home-based training (M3) and at two follow-up points in time (M4: 6 months after M1 and M5: 12 months after M1). All investigations and thus the assessment of the primary and secondary outcomes are performed in a standardised order: questionnaires – clinical examination – biomechanics. Whilst all biomechanical assessments (including the primary outcome) are assessed at each visit, the clinical examination and questionnaires are assessed in a sequenced order. The experimental procedure is shown in detail in Fig. 1 and Additional file 1. Although the measurement periodization is defined, an individual tolerance time of 7 days (M2, M3), 14 days (M4) and 30 days (M5) is set.

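### The primary gain-score comparison is valid, but it leaves out M1 strength and site as covariates and so is generally less precise than it could be

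*Protocol article*

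**What the plan says.** The Statistical analysis section of the protocol article specifies "a gain score analysis (change score analysis) using the mean difference between M1 and M3" for comparing the groups on the primary outcome. It names no covariate for this test. The next paragraph turns to the remaining time points and the secondary outcomes. It lists possible mediators and confounders there: physical activity, psychosocial scores, age, gender, initial pain and body weight. Neither M1 strength nor site is on the list. The significance level is fixed in the same section: "The one-sided a priori level of significance is set at α = 0.025 for all statistical analyses".

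Other sections show that the data for an adjusted analysis will exist:

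- Experimental procedure: "all biomechanical assessments (including the primary outcome) are assessed at each visit", so every participant should have an M1 value.
- Randomization procedure and blinding: allocation follows completion of the first visit, so M1 strength is a true baseline covariate. Each site works from its own lists, with 2:1 blocks of 18.
- Torque/strength: four sites measure isokinetically and two isometrically.

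Under Sample size determination, the pilot effect of 0.24 comes from the change between baseline and 12 weeks, and "effect size was conservatively completed to d = 0.2". The calculation makes no allowance for the correlation between M1 and M3.

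**The concern.** Subtracting M1 from M3 is the same as adjusting for M1 with the slope fixed at 1. In a maximal-effort test with measurement error, the slope of M3 on M1 is often below 1. The change score then over-corrects, and part of the baseline variation stays in the error term. Estimating the slope removes that part.

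Site is a second source of avoidable noise. Lists are issued by site, so site is in effect a stratification factor, and it also determines the device. The primary test as described uses neither fact.

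What is at stake is precision: a wider confidence interval and somewhat less power than the same patients could give, against a small target effect of d = 0.2.

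**Working it through.** **Inputs from the protocol article.** One-sided alpha 0.025, beta 0.1, d = 0.2, allocation 2:1, 791 + 395 = 1186 evaluable, normality and equal variances assumed. **Not in the documents:** rho, the M1–M3 correlation of strength. A range is assumed.

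**1. Reproducing the plan's figure.** With 2:1 allocation the control group needs (1 + 1/2) × (1.960 + 1.282)² / 0.2² = 394.03, rounded up to 395. The intervention group then needs 790, for a total of 1185. The stated 1186 is reproduced to within one patient. Power at 791/395 is Φ(0.2/√(1/791 + 1/395) − 1.96) = Φ(3.246 − 1.96) = 90.1 % (90.04 % by the noncentral t). The planned size therefore matches a plain two-group comparison of changes.

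**2. Variance ratio.** Let the SD be σ at both visits, with a common slope across arms.

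- Change score: 2σ²(1 − rho)
- M3 adjusted for M1: σ²(1 − rho²)
- Ratio, adjusted to change score: (1 + rho)/2

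**3. Effect on size and power**, taking d = 0.2 on the SD of the change. Power = Φ(3.246/√ratio − 1.96).

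| rho (assumed) | variance ratio | N for 90 % power | power at 1186 |
|---|---|---|---|
| change score | 1.00 | 1185 | 90.1 % |
| 0.5 | 0.75 | 888 | 96.3 % |
| 0.6 | 0.80 | 948 | 95.3 % |
| 0.7 | 0.85 | 1005 | 94.1 % |
| 0.8 | 0.90 | 1065 | 92.8 % |
| 0.9 | 0.95 | 1125 | 91.5 % |
| 0.95 | 0.975 | 1155 | 90.8 % |

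If d was standardised by the raw-score SD instead, the absolute N changes but the ratio does not. At rho 0.8, for example, 474 for the change score becomes 426, a ratio of 0.90.

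**4. Unequal SDs.** Let the M3 SD be k times the M1 SD. The ratio becomes k²(1 − rho²)/(1 + k² − 2·rho·k), which equals 1 when the slope rho·k is 1. With k = 1.1:

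- rho 0.8: 1.21 × 0.36/(2.21 − 1.76) = 0.4356/0.45 = 0.968, a saving of 3 % instead of 10 %.
- rho 0.9: 1.21 × 0.19/(2.21 − 1.98) = 0.2299/0.23 = 0.9996, essentially no saving.

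**5. Adding site.** A simulation used six sites, blocks of 18, 2:1 allocation and assumed site shifts, with 800 runs per setting. Adding site to M1 lowered the SE relative to the change score from 0.874 to 0.865 (rho 0.5), 0.956 to 0.948 (rho 0.8) and 0.980 to 0.962 (rho 0.9). Rejection under the null was 2.0 % to 3.4 % with M1 and site in the model, which shows no systematic inflation. The site gain depends on the assumed shifts.

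**6. Slopes that differ between arms, 2:1 allocation.** Take assumed slopes 0.85 (intervention) and 1.05 (control), M1 SD 1 and residual SD 0.3. The pooled slope is (791 × 0.85 + 395 × 1.05)/1186 = 0.917.

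- Adjusted, no interaction: (0.067² + 0.09)/791 + (0.133² + 0.09)/395 = 3.92 × 10⁻⁴
- Change score: (0.15² + 0.09)/791 + (0.05² + 0.09)/395 = 3.76 × 10⁻⁴

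Here the adjusted estimate has about 4 % larger variance.

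**The case against.** The best defence is that nothing is wrong. A gain score is valid under randomisation, it matches the quantity used for the sample size, and it has the planned 90 % power at 1186. That stands: the point is about efficiency only.

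A second defence is that the absence of adjustment is read from silence. Change regressed on group and M1 gives the same group estimate as M3 regressed on group and M1, so the term gain score does not strictly exclude adjustment. The Discussion also promises analyses with co-variables because the population is heterogeneous, and a covariate list may sit in an analysis plan that is not shown. This carries some weight. Still, the article does state the primary method, and its covariate list stands with the other analyses and omits both M1 strength and site.

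Three stronger readings are tempting, and the documents do not support them.

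- **That chance baseline imbalance biases the test.** Over randomisations it does not. In a given trial only (1 − slope) of an imbalance remains. At 1186 one standard error of the M1 difference is 0.062 SD, and a slope of 0.9 lets through about 0.006 SD. The variance ratio already counts this.
- **That adjustment is always at least as efficient and free of any downside.** Step 6 is a counterexample under 2:1 allocation without an interaction. It is a narrow case, since the slopes must lie on opposite sides of 1, but it rules out a guarantee. One common M1 slope may also fit poorly across isokinetic and isometric sites: site terms align levels, not scale.
- **That the gain score leaves the trial underpowered.** A figure of 87.2 % arises if 30 % of 1542 drop out, leaving about 1079. That comes from how the dropout allowance was added (1186 × 1.3), which is a separate matter, and from analysing completers only, whereas the protocol plans multiple imputation.

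**Conclusion.** The point holds as a matter of precision. The primary analysis as described is valid but generally less efficient than one adjusted for M1 strength and site, both known before allocation. With equal SDs and a common slope, and rho assumed between 0.5 and 0.9, the variance falls by 25 % to 5 %.

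The lower end of that saving deserves weight. Mixing men, women, athletes and two measurement types makes large between-person variation, and hence a high rho, plausible. A larger SD at M3 would shrink the saving further, possibly to nothing. No claim of bias or of an inflated type I error follows. The change is worth making because it is cheap, even though its benefit cannot be fixed from the documents.

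**What to change.** Before unblinding, define the primary analysis as a linear model of M3 strength on group, M1 strength and site, with these details:

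- Let the M1 slope differ by device type (isokinetic or isometric).
- Because allocation is 2:1, include a centred group-by-M1 term, or use robust standard errors, if slopes differ between arms. The interaction term addresses the efficiency loss; robust errors only keep the inference valid.
- Report the adjusted group difference with its 95 % CI, tested at one-sided 0.025.
- Keep the gain score as a sensitivity analysis.

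If a separate analysis plan already specifies this, the article's description only needs to be aligned with it.

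The cost is a short addition to the analysis section and slightly more modelling. No new data are needed. Degrees of freedom used are one for M1, five for six sites, and one each for the device-specific slope and the group-by-M1 term. That is at most eight of the 1184 left by a two-group comparison.

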A further potential explanation for the lack of consistent evidence for the beneficial impact of physical activity on nonspecific back pain may be that the impact of physical activity on pain is moderated by contextual and individual psychological and social factors (so-called yellow flags [12]). A better understanding of the role of these moderating factors is crucial to evaluate the role of physical activity for the treatment of chronic back pain and eventually enable the personalization of such physical activity interventions. Individualizing the sensorimotor therapy with respect to individual skill level, demands, preferences, and potential moderating factors such as pain, physical activity, pain experience, stress, life context and the medical care context may lead to greater therapy success [12]. Likewise, determining the optimal dose for treating patients as individuals is still a matter of debate [13, 14].

Against the background of the need for further evidence for the efficacy or non-efficacy of motor control exercise targeting neuromuscular factors like kinematics, strength, postural control and pain [11], the purpose of this study is to test (1) the feasibility and (2) the efficacy of individualized motor control interventions in nonspecific low back pain patients. We hypothesize that individualized motor control exercises lead to an improvement in motor function, assessed as maximal back extension torque, in low back pain patients and in comparison to a control group. Secondary research questions are: (1) does individualized motor control exercises lead to an improvement in motor function, pain and/or pain-related variables in low back pain patients and compared with a control group at short and/or long term and (2, exploratory) to what extent do moderating factors play a role in non-responder detection dose-response considerations and therapy individualization?

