#### Questionnaires – assessment of back pain and moderating factors

At each measurement day (M1-M5) a psychometric assessment is performed to detect the moderating factors (‘yellow flags’) for the chronification of back pain. The test battery will be rotated (Fig. 1) and is partially based on subscales in order to reduce the burden for participants. Pain is assessed by the Chronic Pain Grade questionnaire (CPG) [16], which allows a differentiation in the subscales pain intensity (PI: 0 = “no pain” to 100 = “the worst pain imaginable”), and disability (DS: 0 = “no disability” to 100 = “I was incapable of doing anything”) in the past 3 months. Furthermore, participants can get classified into one of the four hierarchical pain and disability grades ranging from low pain/disability (grade I) to high pain/disability scores (grade IV) [17].

The five moderating factors were assessed using the following psychometric instruments: (1) physical activity: International Physical Activity Questionnaire (IPAQ) [18] and type of physical activity. (2) Pain experience: pain-related cognitions by the Fear-Avoidance Beliefs questionnaire (FABQ-D, [19]), avoidance‐endurance‐behaviour by the Avoidance-Endurance Questionnaire (AEQ; [20] and anxiety and depression by the Hospital Anxiety and Depression Score (HADS-D; [21]) ). (3) Stress: chronic stress by the Trier Inventory of Chronic Stress (TICS; [22]) and critical life events in the last 3 months. (4) Personal life context: social support by the Berlin Social Support Scales (BSSS; [23], individual attachment style by the Relationship Questionnaire 2 (RQ‐2; [24, 25]) as well as the socioeconomic status (CASMIN; [26] and lifestyle (alcohol, smoking, general health and sleeping status). (5) Medical care context: health services options (see also DSF, [27]) .

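### The protocol asks which factors moderate the treatment effect, but the analysis section names only mediation or covariate adjustment, and neither estimates effect modification

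*Protocol article*

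**What the plan says.** The Background of the protocol article gives moderation as part of the rationale: it suggests that "the impact of physical activity on pain is moderated by contextual and individual psychological and social factors". The second of its secondary questions, marked exploratory, asks "to what extent do moderating factors play a role in non-responder detection dose-response considerations and therapy individualization".

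The section on questionnaires carries the same term into data collection: "The five moderating factors were assessed using the following psychometric instruments". The domains are physical activity, pain experience, stress, personal life context and medical care context. Age, sex and body weight are not listed among them.

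The Statistical analysis section changes the term. Its subject is "Potential mediators and confounders like the amount of physical activity, psychosocial scores, age, gender, initial pain level and body weight", and these "will be analysed using multiple regression mediating analyses [35] or included into variance analyses as covariates". The demographic and baseline items thus stand directly before the mediation method: "age, gender, initial pain level and body weight will be analysed using multiple regression mediating analyses". It then details the first option: "For mediation analyses, total as well as direct and indirect effects are calculated", with Sobel testing and a bias-corrected bootstrap of 10,000 subsamples for the indirect effect. It names no analysis of moderation.

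Under the heading on randomisation and blinding, patients are randomised after completing the first visit, so values taken at M1 precede randomisation.

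**The concern.** A moderator, a mediator and a confounder are three different things, and each needs its own analysis. A moderator changes the size of the treatment effect and is studied through a group-by-factor interaction. A mediator is changed by treatment and in turn changes the outcome, so it must be measured after randomisation. In a randomised comparison, a baseline prognostic variable is a candidate covariate.

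The article asks for the first and names methods for the other two. This is more than an omitted detail, because the method is specified down to the test and the number of bootstrap samples, and it does not match the question asked. If the paragraph is followed literally, the trial could report direct and indirect effects for its questionnaire scores and still have no estimate of who benefits more or less. An indirect effect reported for a trait fixed before randomisation would describe only chance imbalance between the groups.

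**Working it through.** **Inputs from the protocol article.** Sample size determination: 1186 patients for analysis, 791 intervention and 395 control, d = 0.2, α = 2.5 %, β = 0.1, ratio 2:1. Statistical analysis: one-sided testing.

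**The plan's own figure.** With one-sided α = 0.025 and 90 % power, the control group needs (1 + 1/2) × (1.960 + 1.282)² / 0.2² = 394.03, rounded up to 395. The intervention group is then 2 × 395 = 790, total 1185 against the stated 1186. The figure reproduces. It serves here only to set the size of the illustration.

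**Assumed values (not in the documents).** A baseline factor M with SD 1, independent of group T; residual SD 1; Y = 0.2·T + 0.3·M + 0.2·T·M + error. The factor therefore moderates the effect by 0.2 SD per SD.

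**What mediation estimates.** The indirect effect is a × b, where a is the group difference in M and b is the slope of Y on M given T.
- Since M precedes randomisation, the expected value of a is 0.
- Without an interaction term, b is about 0.3 + 0.2 × 791/1186 = 0.433.
- The expected indirect effect is 0 × 0.433 = 0, whatever the size of the interaction.
- The Sobel statistic is ab / √(a²·SE_b² + b²·SE_a²). SE_b is about 1/√1186 = 0.029, so b/SE_b is about 15, and the statistic is close to a/SE_a. It is in effect a test of baseline imbalance in M, with about 5 % rejections at a two-sided 5 % level.

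**What a covariate main effect estimates.** It gives b, the average relation of M to the outcome. It carries no information on whether the treatment effect varies with M.

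**What an interaction estimates.** The standard error of the T·M coefficient is √(1/791 + 1/395) = 0.0616. For 0.2, z = 0.2/0.0616 = 3.25 and power is Φ(3.25 − 1.96) = 0.90.

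**Simulation under the same values (3000 trials).** Mean indirect effect 0.0005 (true value 0); Sobel rejects in 4.9 %. Mean interaction estimate 0.199 (true value 0.2); rejects in 89.9 %.

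**Range over the assumed interaction** (power from the formula above):

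| Interaction (SD per SD) | z | Power of interaction test |
|---|---|---|
| 0.10 | 1.62 | 37 % |
| 0.15 | 2.43 | 68 % |
| 0.20 | 3.25 | 90 % |
| 0.25 | 4.06 | 98 % |

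**Range over the assumed slope.** In further simulations of 3000 trials each with interaction 0.2, Sobel rejected in 4.9 % with control-arm slope 0.3, in 3.1 % with control-arm slope 0, and in 0 % when the slope averaged over both arms was exactly 0. It stayed at or below its nominal rate in all three.

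**The case against.** The strongest reply is that the sentence pairs two roles with two methods. Its second half, "or included into variance analyses as covariates", lets age, sex, initial pain and body weight be read as the confounders, entered as baseline covariates. That is legitimate. The repeatedly assessed activity and psychosocial scores would then be the candidate mediators, for which mediation analysis is also legitimate. This reading is open and partly disposes of the matter. What stands is that the sentence does not say which variable gets which method, and that on either reading the moderation question has no matching analysis.

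A reader might go further in three ways that the document does not support.
- **That the moderator question is to be answered by mediation through age or gender.** No section says so. These traits are not among the five declared domains, and the link between the mediation paragraph and the exploratory question is an inference. The Individualization section also describes a separate route to potential non-responders, through questionnaire cutoffs.
- **That group comparisons will be biased by adjusting for values measured after randomisation.** The document does not say which visit supplies the covariates, and initial pain is explicitly a baseline value. The risk arises only if later values are used.
- **That mediation testing would produce excess false findings.** A rejection rate near 5 % is simply the nominal rate.

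It can also be said that interaction terms belong in a fuller plan that is not shown, and that the general wording on regression and variance analyses does not exclude them. Absence alone would indeed be no finding. The finding is that the article does specify a method and that it fits a different question.

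**Conclusion.** The point holds as a mismatch between question and method in an exploratory part of the plan. The article asks about moderation, relabels an overlapping set of factors as mediators and confounders, and names only mediation or covariate entry. Neither can show effect modification, and the undivided list permits mediation through traits whose expected indirect effect is zero by design.

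That an indirect effect through a pre-randomisation variable is zero follows from randomisation and needs no assumed effect size. The contrast of about 5 % against about 90 % does depend on the assumed slope and interaction. It illustrates the distinction and does not measure harm to this trial. Body weight belongs among the fixed traits only as its M1 value, since a later weight could be affected by treatment.

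The primary gain-score comparison and the sample size are untouched. The change is worth making but is not critical.

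**What to change.** Rewrite the paragraph on mediators and confounders in the Statistical analysis section so that each variable is assigned a role.

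- **Moderators:** for each factor measured at M1, fit group, factor and group-by-factor interaction. Report the interaction with a two-sided 95 % confidence interval, since no direction is hypothesised, and label it exploratory.
- **Covariates:** use only M1 values in between-group comparisons.
- **Mediators:** limit mediation analysis to variables measured after randomisation and before the outcome, for example an M2 value with an M3 outcome, also labelled exploratory.

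The questionnaire battery is rotated across visits, so the assignment has to be checked against the visit schedule to see which scores exist at M1 and M2.

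The cost is one rewritten paragraph and some additional exploratory analyses on data already being collected. Two limits should be stated with the results: power is low for small interactions (about 37 % for 0.10 SD per SD under the assumptions above), and testing several factors brings multiplicity.
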